### Inclusion criteria

Aged 18-75 of either sex with a clinical diagnosis of asthma, FEV1 ≥ 60% predicted and an increase in FEV1 of greater than 12% following inhaled salbutamol 400μg or PEF variability >12% during run-in. Allowed medication: 0-800μg inhaled beclomethasone diproprionate or equivalent and as required short acting beta agonist.

### Exclusion criteria

Inability to produce sputum on induction, current smoking, >10 pack years smoking history, treatment with long acting beta-agonists, leukotriene antagonists or theophylline, liver or cardiovascular disease, oral steroid treatment or exacerbation within 6 weeks, females who are pregnant, lactating or not using adequate contraception, any contra-indication to pioglitazone (hypersensitivity to pioglitazone, cardiac failure, history of cardiac failure, hepatic impairment, diabetic ketoacidosis), oral or insulin treatment for diabetes, treatment with gemfibrozil or rifampicin or lactose intollerance.

### Expected duration of participant participation

Study participants will be participating in the study for 18 weeks.

### Removal of participants from therapy or assessments

Subjects may be withdrawn from the trial either at their own request or at the discretion of the Investigator. The subjects will be made aware that this will not affect their future care. Subjects will be made aware (via the information sheet and consent form) that should they withdraw the data collected to date cannot be erased and may still be used in the final analysis.

Data will be collected on reasons for and timing of discontinuation/withdrawal.

Enrolled participants who are not yet randomised will be replaced but participants who withdraw after randomisation will not be replaced.

Abrupt termination of study treatment is not anticipated to affect participant safety.

### Informed consent

All subjects will provide written informed consent. The Informed Consent Form will be signed and dated by the subject before they enter the trial. The Investigator will explain the details of the trial and provide a Participant Information Sheet, ensuring that the subject has sufficient time to consider participating or not. The Investigator will answer any questions that the subject has concerning study participation.

Informed consent will be collected from each subject before they undergo any interventions (including physical examination and history taking) related to the study. One copy of this will be kept by the subject, one will be kept by the Investigator, and a third will be retained in the patient’s hospital records.

Should there be any subsequent amendment to the final protocol, which might affect a subject’s participation in the trial, continuing consent will be obtained using an amended Consent form which will be signed by the subject.

## TRIAL / STUDY TREATMENT AND REGIMEN

*Pre-study consent visit*

Detailed verbal and written information will be provided in clinic or in the clinical sciences building and interested subjects will be asked to sign the consent form and return for a screening visit. Subjects will be askedto withhold inhaled -agonists for 6 hours beforeeach visit and caffeine-containing food and drink from the previousmidnight.

*Screening visit*

At the screening visit, the inclusion and exclusion criteria will be checked as part of the medical history followed by clinical examination and measurement of body mass index. Venesection will be performed for full blood count, liver function test, random glucose and if the patient agreees a single additional EDTA sample will be taken (approximately 10mls) at the same time to prepare plasma to store in the laboratory for future testing in respiratory research studies. We will seek prior patient consent at the pre-study clinic visit as an ‘opt-in’ item on the patient consent form, for permission to save a sample of their plasma in the laboratory to permit future testing of novel biomarkers. This will be fully explained in the patient information leaflet and in person and collection would occur at the same time as venepuncture for safety monitoring. The blood sample will be taken by an experienced doctor or research nurse and cells from the blood will be discarded and no genetic testing will be performed on the stored plasma. Subsequently spirometry (Vitallograph; Buckingham, UK) with measurement of the FEV1 reversibility twenty minutes following administration of 400µcg of inhaled salbutamol via a spacer device (VolumaticTM, Allen and Hanburys UK) followed by sputum induction will be performed.

*Run-in period*

Subjects will enter a two week run in period to complete a diary of their morning and evening peak flow, asthma medication use, nocturnal awakenings and other asthma symptoms.

*Randomisation*

Subjects fulfilling all inclusion criteria with no exclusion criteria will enter the study and allocation to treatment order will be by a computer generated randomization list prepared by the Clinical Trials Unit, Nottingham University, with treatment allocated by an independent pharmacist.

*Treatment period*

Subjects will start treatment with 30mg pioglitazone or placebo daily, increasing to 45mg daily after 4 weeks for the remaining 8 weeks of treatment. Participants will attend for data collection at the same time of day +/-1.5 hours at 0, 4, 8, 12 and 16 weeks within 3 days of the protocol date.

*Data collection*

*Baseline*

The inclusioncriteria will be checked again, 30 mg of trial medication or placebo dispensed as per randomisation code. Diary cards will be checked (symptoms and PEF), use of medication confirmed and adverse effects recorded. The Juniper asthma control and asthma quality of life questionaires completed in the validated paper format followed by measuement of body mass index and clinical examination. Subsequently exhaled nitric oxide, spirometry, methacholine challenge for PD20 and induced sputum will be measured.

*Week 1*

Patients will be contacted by the research team by telephone one week following randomisation to ensure there are no early problems with trial medication or diary card monitoring.

*Weeks 4 and 8*

Diary cards (symptoms and PEF) will be checked, use of medication confirmed, adverse effects recorded then 45mg of trial medication or placebo will be dispensed according to radomisation code at week 4 and week 8. Subsequently measuement of body mass index, clinical examination and spirometry performed. Venesection for liver function tests and random glucose will be performed at week 4.

*Week 12*

At week 12 the treatment phase of the study has ended. Diary cards (symptoms and PEF) will be checked, use of medication confirmed, adverse effects recorded, Juniper asthma control questionnaire and asthma quality of life questionnaire completed. Subsequently clinical examiation, body mass index, measurement of exhaled nitric oxide , spirometry, methacholine challenge, induced sputum and venesection for full blood count, liver function test and glucose in that order.

*Week 16 (Observation)*

Diary cards (symptoms and PEF) will be checked, adverse effects recorded. Subsequently the Juniper asthma control questionnaire, asthma quality of life questionnaire completed and spirometry performed.

### Compliance

Compliance will be assessed by review of diary cards and counting of returned medication.

### Accountability for drugs & placebos

Dispensing will occur from pharmacy and dates and quantities recorded in each participant’s CRF. Dates and quantities of returned medication will also be recorded and confirmation of destruction or return of partially used/unused supplies recorded in pharmacy and CRF.

### Management of study drug overdose

Specific antidotes are not available. General appropriate supportive measures should be used with discussion with the local poisons advice centre if appropriate.

### Criteria for terminating trial

Since this is a pilot study we do not anticipate obtaining data before completion of the study that would lead to its discontinuation. For individual participants, discontinuation will be decided on an individual basis.

#

# STATISTICS

### Methods

The findings will be evaluated by [name], [name], [name], [name], [name] and [name].

The analysis of the Primary response variable (FEV1 at 12 weeks) will be performed using a General Linear Model incorporating terms for baseline value, treatment arm, stratum, and baseline characteristics which are thought *a priori* to strongly predict outcome.

Secondary response variables will be treated similarly, after transformation to approximate Normality as required (as, for example with PD20, Percentage eosinophil count and exhaled NO concentrations). Mean morning and evening PEFR and the percentage of days and nights free of symptoms and relief inhaler use will be calculated for the 14 days prior to each visit and analysed as above. All analyses will be performed using Stata v10.

No interim or sub-group analyses are planned.

Full details will be given in a separate Statistical Analysis Plan to be approved before data lock.

### Sample size and justification

Assuming the SD of differences in FEV1 over 8 weeks is 25035 a study with 88 participants will allow us to detect a difference between treatment arms in the mean 12 week FEV1 of 150 ml with 80 % power at a 5% two-sided significance level. (Stata v10). In practice we aim to recruit 100 subjects to allow for drop-outs.

### Assessment of efficacy

Primary and secondary efficacy endpoints detailed above.

### Assessment of safety

Safety endpoints detailed above.

### Procedures for missing, unused and spurious data

Missing, unused and spurious data will be reported as such in the ensuing publication.

### Definition of populations analysed

Safety set: All randomised participants who receive at least one dose of the study drug.

Full Analysis set: All randomised participants, who take at least one dose of study medication and for whom at least one post-baseline assessment of the primary endpoint is available.

Per protocol set: All participants in the Full Analysis set who are deemed to have no major protocol violations that could interfere with the objectives of the study.

Efficacy will be assessed on both the full analysis set and the per protocol set. Safety summarises will be performed on the safety set.

# ADVERSE EVENTS

### Definitions

An adverse event is any unfavourable and unintended sign, symptom, syndrome or illness that develops or worsens during the period of observation in the study.

An AE does include a / an:

1. exacerbation of a pre-existing illness.

2. increase in frequency or intensity of a pre-existing episodic event or condition.

3. condition detected or diagnosed after medicinal product administration even though it may have been present prior to the start of the study.

4. continuous persistent disease or symptoms present at baseline that worsen following the start of the study.

An AE does not include a / an:

1. medical or surgical procedure (e.g., surgery, endoscopy, tooth extraction, transfusion); but the condition that lead to the procedure is an AE.

2. pre-existing disease or conditions present or detected at the start of the study that did not worsen.

3. situations where an untoward medical occurrence has not occurred (e.g., hospitalisations for cosmetic elective surgery, social and / or convenience admissions).

4. disease or disorder being studied or sign or symptom associated with the disease or disorder unless more severe than expected for the participant’s condition.

5. overdose of concurrent medication without any signs or symptoms.

A Serious Adverse Event (SAE) is any adverse event occurring following study mandated procedures, having received the IMP or placebo that results in any of the following outcomes:

1. Death

2. A life-threatening adverse event

3. Inpatient hospitalisation or prolongation of existing hospitalisation

4. A disability / incapacity

5. A congenital anomaly in the offspring of a participant

Important medical events that may not result in death, be life-threatening, or require hospitalisation may be considered a serious adverse event when, based upon appropriate medical judgment, they may jeopardize the patient or participant and may require medical or surgical intervention to prevent one of the outcomes listed in this definition

All adverse events will be assessed for seriousness, expectedness and causality:

A distinction is drawn between serious and severe AEs. Severity is a measure of intensity whereas seriousness is defined using the criteria above. Hence, a severe AE need not necessarily be serious.

### Causality

**Not related or improbable**: a clinical event including laboratory test abnormality with temporal relationship to trial treatment administration which makes a causal relationship incompatible or for which other drugs, chemicals or disease provide a plausible explanation**.** This will be counted as “unrelated” for notification purposes.

**Possible**: a clinical event, including laboratory test abnormality, with temporal relationship to trial treatment administration which makes a causal relationship a reasonable possibility, but which could also be explained by other drugs, chemicals or concurrent disease. This will be counted as “related” for notification purposes.

**Probable**: a clinical event, including laboratory test abnormality, with temporal relationship to trial treatment administration which makes a causal relationship a reasonable possibility, and is unlikely to be due to other drugs, chemicals or concurrent disease. This will be counted as “related” for notification purposes.

**Definite**: a clinical event, including laboratory test abnormality, with temporal relationship to trial treatment administration which makes a causal relationship a reasonable possibility, and which can definitely not be attributed to other causes. This will be counted as “related” for notification purposes.

An AE whose causal relationship to the study IMP is assessed by the Chief Investigator as “possible”, “probable”, or “definite” is an Adverse Drug Reaction.

With regard to the criteria above, medical and scientific judgment shall be used in deciding whether prompt reporting is appropriate in that situation.

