### Reporting of adverse events

Participants will be asked to contact the study site immediately in the event of any serious adverse event. All adverse events will be recorded and closely monitored until resolution, stabilisation, or until it has been shown that the study medication or treatment is not the cause. The Chief Investigator shall be informed immediately of any serious adverse events and shall determine seriousness and causality in conjunction with any treating medical practitioners.

In the event of a pregnancy occurring in a trial participant or the partner of a trial participant monitoring shall occur during the pregnancy and after delivery to ascertain any trial related adverse events in the mother or the offspring. Where it is the partner of a trial participant consent will be obtained for this observation from both the partner and her medical practitioner.

All serious adverse events will be recorded and reported to the MHRA and REC as part of the annual reports. SUSARs will be reported within the statutory timeframes to the MHRA and REC as stated below. The Chief Investigator shall be responsible for all adverse event reporting.

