## SUSARs

**A serious adverse event that is either sudden in its onset, unexpected in its severity and seriousness or not a known side effect of the IMP *and* related or suspected to be related to the IMP is classed as Suspected Unexpected Serious Adverse Reaction and requires expedited reporting as per the clinical trials regulations.**

**All serious adverse events that fall or are suspected to fall within these criteria shall be treated as a SUSAR until deemed otherwise.**

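### The causality scale places an event with compatible timing and a plausible alternative cause in both 'Not related or improbable' (unrelated) and 'Possible' (related), with no tie-break

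*Protocol*

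**What the plan says.** The Protocol, Adverse Events, Causality, defines four ratings.

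- **'Not related or improbable'** applies when the timing is one "which makes a causal relationship incompatible or for which other drugs, chemicals or disease provide a plausible explanation". Its notification status: "This will be counted as “unrelated” for notification purposes".
- **'Possible'** applies to timing "which makes a causal relationship a reasonable possibility, but which could also be explained by other drugs, chemicals or concurrent disease". Its notification status: "This will be counted as “related” for notification purposes".
- **'Probable'** and **'Definite'** also need timing that makes causation a reasonable possibility. In addition, other causes must be unlikely ('Probable') or definitely ruled out ('Definite'). Both count as related.

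Two rules use the outcome. In the same section, an event "assessed by the Chief Investigator as “possible”, “probable”, or “definite” is an Adverse Drug Reaction". Under SUSARs, a serious and unexpected event that is "related or suspected to be related to the IMP is classed as Suspected Unexpected Serious Adverse Reaction and requires expedited reporting".

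**The concern.** A causality scale should give each event one rating. Here the lowest rating can be reached by two separate routes, and the second asks only for a plausible alternative cause. 'Possible' asks for reasonable timing together with an alternative cause. Two assessors looking at the same event could apply the text faithfully and reach opposite notification statuses.

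Two things are at stake. The first is which events are labelled Adverse Drug Reactions, in a trial that lists recording adverse effects among its purposes. The second is whether an unexpected serious event is reported on an expedited basis. The permissive reading errs toward under-reporting. The protocol fixes these definitions itself and notification runs from them, so this is not a matter left to a statistical analysis plan.

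**Working it through.** No figure is involved. The check is whether the four definitions are mutually exclusive and cover every case. Cross the two attributes that the definitions use: timing (causation incompatible, or a reasonable possibility) and a plausible alternative explanation (present or absent).

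| Timing | Plausible alternative | Ratings met | Status |
|---|---|---|---|
| Incompatible | Present | Not related | Unrelated |
| Incompatible | Absent | Not related | Unrelated |
| Reasonable possibility | Present | Not related (second half of the 'or') **and** Possible | Unrelated **and** related |
| Reasonable possibility | Absent | Probable or Definite | Related |

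One cell of four is doubly assigned. It is the cell that 'Possible' was written for: any event that meets 'Possible' and has a plausible alternative also meets 'Not related or improbable'.

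Could the wording separate the two? The only difference is between an alternative that provides a plausible explanation and one that could also explain the event. No threshold or example turns that into a usable distinction. The Causality section ends by leaving the appropriateness of prompt reporting to medical and scientific judgment, which adds discretion but does not say which rating applies.

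Next, trace what depends on the rating.

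1. *Adverse Drug Reaction status.* The definition lists the three upper ratings, so the ambiguity carries over directly.
2. *SUSAR reporting.* The test needs the event to be related or suspected to be related. The SUSARs section treats suspected cases as SUSARs only until they are deemed otherwise. The Chief Investigator then assesses relatedness, and the Causality section supplies the only scale for doing so. An event kept as a SUSAR goes to the MHRA and the ethics committee within seven days. If it is rated unrelated, what remains is the annual report of all serious events described under Reporting of adverse events.
3. *Follow-up.* Reporting of adverse events requires every adverse event to be monitored until it resolves, stabilises, or "until it has been shown that the study medication or treatment is not the cause". That rule does not mention the ratings.

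**The case against.** The strongest reply is that the literal reading cannot be the intended one, because it would absorb essentially the whole of 'Possible'. On a natural reading, 'Not related or improbable' covers events that another cause accounts for, and 'Possible' covers events where both explanations remain open. That is probably what was meant. It stands as a guess at intent, but the protocol does not say it, and the scale has to be applied as written.

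A second reply is that there are safeguards. Suspected SUSARs are treated as such until decided otherwise, causality is settled together with treating practitioners, all serious events reach the annual reports, and the data monitoring committee can see all study data and unblind. These stand and limit the harm. They do not remove the ambiguity at the point where relatedness is decided.

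A reader might also infer more than the documents support:

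- *That an unrelated rating ends follow-up.* It does not. Monitoring applies to all adverse events, and showing that the drug is not the cause is a higher bar than having another explanation available.
- *That the safety comparison between arms is compromised.* The Safety endpoints section counts adverse effects by how they were reported, and the safety summaries use the safety set. Neither filters by causality, no stated endpoint is a count of Adverse Drug Reactions, and outcome assessors are blinded.
- *That nearly every event here is affected, because all participants have asthma.* The Definitions section already keeps symptoms of the studied disease out of adverse events unless they are worse than expected. Nothing in the protocol says that asthma would explain, for example, a change in the liver tests or glucose that it monitors.

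**Conclusion.** The concern holds as an internal inconsistency in the Causality section. One of four combinations of timing and alternative cause receives two ratings with opposite notification statuses, and no tie-break is given. The direct consequence is inconsistent labelling of Adverse Drug Reactions. The more serious one is conditional: an unexpected serious event with compatible timing and a plausible alternative cause could be reported annually instead of within seven days, if the assessor uses the second half of the 'or'. The event would still be recorded as an adverse event.

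The documents give no share of events with compatible timing and an alternative cause, so no percentage can be attached to the problem. The conclusion rests on the plain wording and on treating a plausible explanation and one that could also apply as the same thing, since the protocol gives no way to tell them apart. The primary endpoint, sample size and efficacy analysis are not affected.

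**What to change.** Amend the two definitions together so that each event falls into exactly one rating:

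- 'Not related or improbable' applies when the timing makes a causal relationship incompatible or improbable, whether or not an alternative explanation exists.
- An alternative explanation alone does not suffice for that rating.
- An event with compatible timing and a plausible alternative explanation is 'Possible' and counts as related.

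Simply replacing 'or' with 'and' in the first definition would not do. An event with incompatible timing and no known alternative cause would then fit no rating, because the other three all need reasonable timing. That would exchange an overlap for a gap.

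The cost is a short protocol amendment and somewhat more events counted as related.
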